## Abstract

**Background:**

The transition from pediatric to nephrology care is not yet a standardized procedure. The result is an increased risk of deteriorating transplant function, with the potential for premature transplant failure.

**Methods/Design:**

In phase I of this study, we shall evaluate the current patient transition situation in all existing German pediatric and nephrology departments (n = 17), including an evaluation of the views of physicians, nurses, and psychosocial support staff regarding transition. Phase II will be a prospective, randomized study in which we compare current unstructured transition (control group) to structured transition (intervention group). The structured transition approach integrates the core elements of the Berliner TransitionsProgramm in combination with two facilitating smartphone apps. The primary endpoint of this study will be therapy adherence, as reflected by group variation coefficients of immunosuppressive agent levels. As a secondary outcome, we will compare patients’ self-reported quality of life, satisfaction of patients and their parents with each transition model, and how patient-centered healthcare components are utilized. These secondary parameters will be assessed with established instruments or with instruments developed (and pilot tested) in phase I of the project.

**Discussion:**

The long-term goal of this work is to provide a model of structured transition from pediatric to adult care for adolescent nephrology patients, in order to improve transplant survival and patient wellbeing.

**Trial registration:**

Identifier: Clinicaltrials.gov: ISRCTN22988897, registered on 24 April 2014).

## Background

The transition of chronically ill adolescents from pediatric to adult medicine should conserve or improve their state of health. Such a transition can be considered successful if it promotes the patients’ health competence, supports their psychosocial rehabilitation, and improves their self-determination efficacy, including their ability to make decisions and communicate about their care. The overarching goal of transition is to enable patients to be as independent as possible and have the best possible quality of life. Achieving these goals requires, in addition to addressing medical issues, a multidimensional, multidisciplinary approach, including critical interventions in psychosocial, school-related, and occupational spheres [1].

Historically, a lack of cooperation among the various professionals involved in treatment and concomitant care has led to medical care issues for patients, which is particularly problematic in the transition phase. From an analysis of such deficiencies, it is possible to derive strategies for establishing a satisfactory patient-centered transition [1–4].

In nephrology in particular, the transition constitutes an important intersection in patient care [5, 6]. More transplanted kidneys are lost in patients aged between 16 and 21 years than in any other age group. Such graft failure requires a return to compulsory dialysis, which reduces quality of life and leads to considerable additional healthcare expense. Moreover, early graft losses increase mortality and shorten life expectancy. Some single-center transition models with transitional or adolescence-centered consulting hours (such as the Nephrology adolescent outpatient clinic of the Kuratorium for Dialysis and Transplantation in Hannover) have been established. They represent a new structural model for medical care in which there is a focus on prevention of non-adherence to reduce deterioration of kidney graft failure and, therefore, kidney diseases in this vulnerable age group [7, 8]. Training programs, such as ‘*Finally Grown Up*’ (‘*Endlich-Erwachsen*’) [9] and computer-based training courses [10], have been shown to produce some improvements in the transition of post-kidney transplant adolescents into adult medical care. For instance, the positive effects of ‘patient empowerment’ have been reported for adolescents receiving hyperphosphatemia therapy [11]. At present, it is not clear which, if any, transition models are applied in German pediatric nephrology centers.

The Berliner TransitionsProgramm is the first structured transition program in Germany to be financed by statutory health insurance (Figure 1). It regulates the transition of adolescents with different indications (currently, diabetes mellitus type 1, epilepsy, renal diseases, juvenile rheumatoid arthritis, inflammatory bowel diseases, and neuromuscular diseases) from pediatric to adult medicine over a period of two years. The program outlines the ways in which the course of this transition should proceed. Above all, it contains specific transitional measures for in-depth communication between the pre- and post-transition treating physicians, as well as conversations with adolescent patients and their parents, structured in terms of time and content. A case management protocol is used to support and ensure the unhindered flow of information and application of treatment measures [12].

**Figure 1 Fig1:**
[figure not shown]
**Structure of the Berliner transitions programm.** eCRF, electronic case form.

The introduction of smartphone apps, which can be used to help monitor adolescent patients, may improve their adherence [13]. The rationale for using such apps is to interact with the patients through media that are familiar to them, enabling them to manage their disease even under the challenging conditions of adolescence. A willing acceptance of such high-tech instruments by adolescent patients can support and develop their competency in dealing with the disease.

We hypothesize that a structured transition, namely the Berliner TransitionsProgramm, complemented by telemedicine monitoring via smartphone apps, can facilitate the transition to adult care and improve the therapeutic adherence of adolescent patients living with a transplanted kidney. If correct, such an approach would improve post-transplant functioning and survival, and ultimately improve patient survival and wellbeing.

In this study, therefore, our first aim is to examine how many pediatric nephrology centers in Germany employ a structured transition protocol, and if so, at what point it is initiated. We are documenting the structure of transition plans, including courses of action, the type of participant (such as physicians, psychologists, nurses, or case managers), and the financing of programs based on the study by Bethe and Haffner [14]. In centers without a structured transition protocol, we aim to explore how transitions are organized and why no transition program has yet been initiated. Firstly, we will compare how on-site staff evaluate structured versus unstructured transition of kidney-transplanted adolescents to adult medicine and will conduct surveys on the need for possible improvements. Secondly, by implementing a prospective, multicenter two-arm randomized intervention study, we plan to clarify whether a structured transition program with supplementary smartphone apps can improve the outcome of transitioning patients.

## Methods/Design

### Subjects

The study was approved by the research ethics committee of the Hannover Medical School (approval number: 6660). Informed consent will be obtained from the adolescent patients, as well as from their parents. The study cohort will include male and female patients who have undergone a kidney transplant who were between 16 and 22-years-old at study enrollment. There is a huge variation in age at transition in Germany; several centers make the transfer at 18 years whilst others do not transfer until the age of 22. For inclusion the patient must be: at least 14 months away from expected transfer to adult medical care, at least three months post-transplantation, capable of operating a smartphone, and able to provide informed consent. Exclusion criteria are: signs of acute transplant rejection or indications of a need for dialysis in the foreseeable future (since transplant survival is a study outcome variable), as well as mental incapacity (since it may prevent complete and independent use of the apps). Patients will be randomized into two groups: an intervention group that receives case management by the Berliner TransitionsProgramm, which is supported by a smartphone (Samsung Galaxy Y, Samsung, Seoul, South Korea) with two apps; and a control group transferred according to the established protocols of the center. There are centers in Germany which already practice some kind of transition management, however, no center actually uses smartphone apps or case management. Our interventions can also therefore improve outcome in centers that already practice active transition. Because of the center-based stratification used in this study, patients from German centers actually performing transition will be distributed equally amongst both groups.

### Sample size calculation

We first estimated the likely therapy adherence rate based on a small group of patients on immunosuppressive therapy. Data from Hannover Medical School showed that among six selected patients, three showed very good compliance, with a mean coefficient of variation (%) of 0.13 (±0.03), whereas poor compliance was observed in the three remaining patients, with an average coefficient of variation (%) of 0.5 (±0.03). These values were taken as roughly predictive of the variance we would observe in our study. We will receive additional data from phase I on which to base the sample size assumptions. Assuming a population of 50% with very good compliance, 25% with average compliance, and 25% with poor compliance, we simulated a mixed distribution with the statistical values above and calculated an average coefficient of variation (%) of 0.26, with a standard deviation of 0.15. Our expectation is that the intervention will increase the ratio of patients with good compliance. For that reason we assumed the following positively shifted distribution (%) for the intervention group: 70:30:0 of very good:average:poor compliance. This distribution corresponds to a coefficient of variation (%) of 0.181 with the same standard deviation of 0.15. Assuming a two-sided type I error of 5%, a Student’s two-sample t-test will have 80% power under the planning assumptions if n = 57 patients per group are randomized. Hence, a total of 114 patients must be recruited for this trial. We supposed a negligible dropout rate since it is critical that transplant patients receive ongoing care and attend their treatment centers regularly. In addition, we believe that providing free smartphones will increase adherence. In the unexpected case of too many dropouts, we will extend the recruitment phase to ensure sufficient patients are included in the trial throughout the complete follow-up period.

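### The intervention-arm SD of 0.15 does not follow from the 70:30:0 mixture, which implies about 0.08, so the stated 80% power at 57 per group understates the power of the plan's own model

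*Protocol article*

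**What the plan says.** The section on sample size calculation in the protocol article starts from six selected patients at one hospital. The three good compliers are described "with a mean coefficient of variation (%) of 0.13 (±0.03"), the three poor compliers "with an average coefficient of variation (%) of 0.5 (±0.03"). An average class is also used, but its mean and SD are not given.

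Controls are taken as 50% very good, 25% average and 25% poor. From a simulated mixture the authors "calculated an average coefficient of variation (%) of 0.26, with a standard deviation of 0.15". The intervention arm is shifted to 70% very good, 30% average and no poor compliers, and of this mixture the article says: "This distribution corresponds to a coefficient of variation (%) of 0.181 with the same standard deviation of 0.15". A Student's t-test at a two-sided 5% level "will have 80% power under the planning assumptions if n = 57 patients per group are randomized", which makes 114 in total.

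The text presents 0.15 as a property of the 70:30:0 distribution. Nowhere does it say that 0.15 was kept on purpose as a cautious common value.

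**The concern.** In a mixture of three well-separated narrow classes, nearly all the spread is spread between classes. Removing the class furthest from the others must shrink the SD, yet the article reports the same SD before and after the poor compliers are removed.

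What is at stake is whether the 80% is the power of the distributions that the plan sets out. If it is not, readers are misinformed about what 114 patients can detect. The article also says that phase I data will feed into the sample size assumptions. An update that carried 0.15 forward as the SD of the 70:30:0 mixture would repeat the error.

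**Working it through.** **Inputs (protocol article, sample size calculation).** Very good class: mean 0.13, SD 0.03. Poor class: mean 0.50, SD 0.03. The ± is not labelled and is read here as an SD. Weights: 50:25:25 (control) and 70:30:0 (intervention). Stated arm values: 0.26 and 0.181, SD 0.15 in both. Two-sided 5%, 80% power, 57 per group. The average-class mean *m* and SD *s* are not given. I back-solve *m* from the arm means, assume *s* = 0.03 as in the other classes, and then vary both.

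**1. The plan's own figure.** The difference is 0.26 − 0.181 = 0.079. By the normal approximation, n = 2 × (1.96 + 0.8416)² × 0.15² / 0.079² = 56.6, so 57 per group. The exact t-test gives 79.6% power at 57. The stated number follows from a common SD of 0.15.

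**2. The average class.**
- From the intervention mean: *m* = (0.181 − 0.7 × 0.13) / 0.3 = 0.30.
- From the control mean: *m* = (0.26 − 0.5 × 0.13 − 0.25 × 0.50) / 0.25 = 0.28.

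**3. Mixture SDs.** The variance is Σ w(s² + m²) − mean². With *m* = 0.30 and *s* = 0.03:
- Control: mean 0.265; variance 0.09345 + 0.0009 − 0.265² = 0.0241; SD 0.155. The poor class alone contributes 0.25 × (0.50 − 0.265)² = 0.0138 of this variance.
- Intervention: mean 0.181; variance 0.7 × 0.3 × (0.30 − 0.13)² + 0.03² = 0.00697; SD 0.083.

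With *m* = 0.28 the SDs are 0.154 and 0.075. For *m* from 0.25 to 0.315 and *s* from 0.03 to 0.10, the intervention SD runs from 0.063 to 0.104. Reading ±0.03 as a standard error of three patients (SD 0.03 × √3 = 0.052) gives 0.086 to 0.094.

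**4. Can any average class give 0.15 in both arms?** The control variance is 0.5 × 0.0178 + 0.25(m² + s²) + 0.25 × 0.2509 − (0.19 + 0.25m)². This rearranges to 0.0235 + 0.1875(m − 0.2533)² + 0.25s², so the control SD is never below 0.153. A grid search over *m* and *s* shows that wherever the control SD is below 0.155, and so rounds to 0.15, the intervention SD is at most 0.085. Forcing 0.15 on the intervention arm breaks other stated figures:
- Widening only the average class at *m* = 0.30 needs *s* of about 0.23, and the control SD is then 0.193.
- Widening all classes equally needs a common SD of about 0.128, and the control SD is then 0.199.
- Moving the average class to about 0.45 makes the intervention mean 0.226, not 0.181, and the control SD 0.176.

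**5. Power at 57 per group.** The t-test power uses the root mean square of the two arm SDs. It is shown for the mixtures' own difference in means and for the stated 0.079.

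| *m* | *s* | SD control | SD intervention | Own difference | Power, own difference | Power, 0.079 |
|---|---|---|---|---|---|---|
| 0.28 | 0.03 | 0.154 | 0.075 | 0.085 | 96.0% | 93.1% |
| 0.30 | 0.03 | 0.155 | 0.083 | 0.084 | 94.6% | 91.8% |
| 0.28 | 0.10 | 0.162 | 0.091 | 0.085 | 92.9% | 89.0% |
| 0.30 | 0.10 | 0.162 | 0.098 | 0.084 | 91.1% | 87.5% |
| 0.315 | 0.10 | 0.163 | 0.104 | 0.083 | 89.6% | 86.3% |
| 0.30 | 0.15 | 0.172 | 0.116 | 0.084 | 85.8% | 81.4% |

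Simulating the mixtures themselves with *s* = 0.03 (40,000 runs) gives 95.5% for *m* = 0.30 and 97.1% for *m* = 0.28, so the t-based figures are not flattering.

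**The case against.** The best defence is that a common SD is the usual input to a Student's t-test, that 57 per group follows from it, and that the error is conservative. All of this stands. One sentence declaring 0.15 a cautious common value would remove the contradiction. It does not rescue the text as written, which derives 0.15 from the 70:30:0 mixture.

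It is also fair that the recalculated power is no firmer than its inputs. They come from six selected patients and an average class that is not described. With *s* = 0.15 and the stated difference, power falls to 80-84% for *m* from 0.25 to 0.315. The control SD is then about 0.17, which departs from the stated 0.15. A single replacement figure such as 95% would therefore claim too much, and a range is needed.

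A reader might infer more than the document supports:
- **That the trial is underpowered or 57 is miscalculated.** The error runs the other way, and 57 is correct for a common SD of 0.15.
- **That recruitment should be cut.** For 80% power the mixtures with *s* = 0.03 need only about 34-36 per group at their own difference, or 39-41 at 0.079. Class values from six patients are too thin to justify a reduction.
- **That the two arm means contradict each other.** An average class at 0.30 gives a control mean of 0.265 against the stated 0.26. A gap of 0.005 is within rounding and simulation error.
- **That unequal variances endanger the planned test.** With equal arms the effect is negligible: simulated normal data with SDs of 0.155 and 0.083 gave type I error of 5.2% for Student's test and 5.1% for Welch's.

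**Conclusion.** The point holds as a wrong stated SD, and with it a wrong stated power, in the primary sample size justification. The SD of the 70:30:0 mixture is about 0.083, roughly half the stated 0.15, and 0.06 to 0.10 over the range examined. That 0.15 cannot hold in both arms does not depend on the unstated average class, given the stated class values and weights.

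The size of the power error does depend on that class. At 57 per group the power is about 92-96% for an average class at 0.28 to 0.30 with SD 0.03. With an SD of 0.10 it is about 86-91% for class means of 0.30 to 0.315, and up to 93% at 0.28. The stated 80% is correct only for 0.15 taken as a common SD. The error is conservative and gives no reason to change the 114 patients.

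**What to change.** Reword the sample size section in three respects:

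- State the mean and SD assumed for the average class.
- Replace the intervention-arm SD with the value that the 70:30:0 mixture implies (about 0.08 under the values used here).
- Restate the power at 57 per group, with its range over plausible average-class SDs.

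If the sponsor prefers to keep 0.15 in both arms, say that it is a deliberately conservative common SD and not a property of the 70:30:0 distribution, and that 80% is lower than the power the mixtures imply. Use arm-level SDs that follow from the model in any update from phase I data.

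The cost is one reworded paragraph, with no change to patient numbers, test or decision rule.

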### Study design

The study is a composite of two phases, as shown in Figure 2. In phase I, which is currently ongoing, we are conducting retrospective and prospective structured data collection and data analysis of the present medical care situation and care providers’ assessments of it. The progress of patients who have been transferred within the last three years and have been receiving medical treatment for at least a year are being collected in a retrospective anonymized manner and evaluated. Additionally, we are developing and piloting data collection tools (questionnaires, interview guidelines, and smartphone apps) for phase II of the study, which consists of an open, prospective, multicenter two-arm, randomized intervention analysis.

**Figure 2 Fig2:**
[figure not shown]
**Overview of study milestones, phases, and timeline.**

### Phase I

A retrospective analysis of the existing structures is carried out on-site at each of 17 pediatric nephrology centers, together with prospective questioning to assess the transition mechanisms. We follow a structured analysis of the existing transition procedures (initiation, beginning, financing, participants, documentation, and experiences) and assess healthcare providers’ views of their current institutional transition protocols based on qualitative (personal) expert surveys. Healthcare provider assessments include three interviews: one with a physician at each center, one with each center’s auxiliary nursing unit, and one with each center’s psychologist or social worker. The interviews are being analyzed in following recommendations made by Mayring [15] to define ways of recruiting subjects for the prospective study.

Information regarding each patient’s medical care and treatment course are registered via an anonymized questionnaire for patients who transferred in the years 2011 and 2012 from all of the participating pediatric nephrology centers, covering before and after the transfer. Treatment course variables include estimated glomerular filtration rate (eGFR), coefficient of variation (%) of immunosuppressive levels, and incidence of acute rejection and transplant loss. Additionally, an online transition questionnaire for physicians and nephrologists is being developed; it will be distributed by the German Society for Nephrology.

### Transfer supporting apps

We will employ apps designed to support the documentation and transfer of clinical data and to facilitate appointment scheduling. The apps are being developed for iOS and Android smartphones, with a diary function in cooperation, with the Children’s Aid Association for Organ Transplantation - Sportsmen for Organ Donation Registration Society (‘*Verein Kinderhilfe Organtransplantation - Sportler für Organspende e.V.*’ *(*KiO)). There is a pre-existing app that, in conjunction with KiO, is being extended for monitoring of clinical values (Kinderhilfe Organtransplantation, Frankfurt, Germany). In addition, a new app to organize appointments and communicate with the case manager will be developed to complement the Berliner TransitionsProgramm (Synectic, Berlin, Germany). The apps are currently being piloted with some patients.

### Phase II

Phase II of the study will be a real world, prospective, multicenter, randomized two-arm intervention, in which an intervention and a control group will be compared. In the control group, adolescents will go through transition as established in their center. In the intervention group, adolescents will be transitioned using structural elements from the Berliner TransitionsProgramm (case manager, transition interviews, and so forth) and with the smartphone apps developed during phase I.

An on-site physician involved in the study will obtain consent from patients that meet the inclusion and exclusion criteria, and also from parents for patients under 18 years of age. Patients will be enrolled at least 14 months before the study termination point and will be randomized into intervention and control groups. Identification of eligible patients began in the first year of the study. The physician continuing with each patient’s medical care will be identified and contact will be established with all receiving physicians for both study groups. Patient and physician addresses are also being registered so that, should there be a change in care providers, contact can be maintained. Patients and family members will be interviewed at two time points using standardized instruments for collecting personal data; these are being developed in phase I of the study. If necessary, available validated tools will be adapted.

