### Time points

The phase II study timeline, summarized in Figure 3, begins with the start of transition and concomitant entry (E) into the study at time point T0 (baseline), and proceeds with a 12-month assessment at time point T1 and a 24-month assessment at time point T2. At T0 we will collect data for each group about each patient’s expectations for the transition, health status, time since transplantation, quality of life, satisfaction with medical care, therapy, adaptation to the disease, healthcare utilization, social environment, education, gender, age, and number of siblings. At T1, both groups will be evaluated for the transition planned, health status, quality of life, satisfaction with medical care, healthcare utilization, therapy system, and adherence. The intervention group will also be asked additional questions at T1 regarding their experience with the smartphone and app and how well they have adopted the program. After the T1 evaluation, each patient will be transferred to their respective adult care nephrologist. The following variables will be assessed at T2: evaluation of the transition, health status, quality of life, satisfaction with medical care, healthcare utilization, therapy system, education, employment, relationship status, and adherence.

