### Study endpoints

The long-term goal of this work is to improve adherence through a controlled transition process. The primary outcome variable of the study is therapy adherence, as indicated by individual variability in immunosuppressive agent levels. Immunosuppressive agent levels will be recorded at all regular follow-up examinations (every four to eight weeks). A coefficient of variation (%) will be calculated for each patient based on these examination data. These coefficient values will serve as a surrogate parameter for patient adherence. The individual coefficient of variation (%) for immunosuppressive agent levels is the endpoint of choice for this field of research [15].

The secondary endpoints of the study are change in pre- and post-transfer eGFR (using the Schwartz 2009 formula [16], Modification of Diet in Renal Disease formula [17], and cystatin-C levels), serum creatinine levels, transplant survival, patient survival, acute rejection reactions (presence of donor-specific antibodies and chronic-humoral rejection), transplant loss, death, patient satisfaction, healthcare utilization, and patients’ self-reported quality of life and social integration.

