### Statistical analysis

The coefficients of variation (%) for immunosuppressive agent levels will be analyzed by analysis of covariance, with adjustment for immunosuppressive agent level at T0 and all stratification variables considered in the randomization, such that the analysis of covariance can be used to determine group differences. [18] Least squares means will be calculated for each group and the difference between the group means will be reported with a two-sided 95% confidence interval (CI). If the upper limit of the CI for the difference between the adjusted means (transition minus standard) for the therapy effect is less than 0, then lower variability in immunosuppressive agent levels and thus better adherence to therapy due to the new transition model is therefore proved. Sensitivity analyses will be carried out using multivariate regression models with consideration of additional prognostic factors (modeling after stepwise variable selection). Secondary dichotomous endpoints (such as transplant loss) will be assessed with multivariate logistic regression models.

All patients included in the study (intention-to-treat population) will be considered in the primary and secondary analyses described above. For patients who suffer a transplant loss, the immunosuppressive agent levels measured before the loss will be used. Using a conservative approach, patients with fewer than three immunosuppressive agent level datum points will be coded with the largest coefficient of variation (%) in their respective therapy group. The study began recruiting patients as from 1 April 2014 (pre-screening).

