## Trial status

Phase I of the study is in progress. Recruitment has started in November 2014 and is expected to finish in November 2015. The healthcare currently in place is being analyzed and the tools to be used in phase II are being reviewed.

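### The 14-month enrolment limit before study termination conflicts with the 24-month T2 assessment and must be reconciled with the 14 months to transfer

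*Protocol article*

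**What the plan says.** All references are to the protocol article.

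- **Phase II** ties enrolment to the end of the study: "Patients will be enrolled at least 14 months before the study termination point".
- **Time points** starts the timeline at entry (T0) and "proceeds with a 12-month assessment at time point T1 and a 24-month assessment at time point T2". On transfer it says: "After the T1 evaluation, each patient will be transferred to their respective adult care nephrologist". Evaluation of the transition, quality of life, satisfaction, healthcare utilization, education, employment, relationship status and adherence are among the variables listed at T2.
- **Subjects** uses the same number with another anchor. An eligible patient must be "at least 14 months away from expected transfer to adult medical care".
- **Study endpoints** bases the primary CV on levels from routine visits 4 to 8 weeks apart and does not restrict it to the period after transfer. The secondary list opens: "The secondary endpoints of the study are change in pre- and post-transfer eGFR". Graft survival is on the same list.
- **Statistical analysis** sets a minimum number of levels: "patients with fewer than three immunosuppressive agent level datum points will be coded with the largest coefficient of variation (%) in their respective therapy group".
- **Trial status** gives the recruitment window: "Recruitment has started in November 2014 and is expected to finish in November 2015".

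The text shown gives no date for study termination.

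**The concern.** The enrolment rule and the visit schedule cannot both be satisfied for every patient whom the rule admits. A site following the Phase II section to the letter could enrol a patient 14 months before the study ends, and that patient's T2 would fall 10 months after closure.

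The trial asks whether structured transition helps patients across the move to adult care, so the months after transfer matter most. For a late enrollee, the T2 questionnaire variables would not exist. The post-transfer side of the eGFR comparison, the graft-survival follow-up and the post-transfer drug levels would be cut short. The primary CV would mix patients observed for different lengths of time. The late enrollees' values would describe mainly the paediatric phase, so any effect that appears only after transfer would be diluted. Questionnaire data not collected before closure cannot be recovered later.

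**Working it through.** **Inputs.** Minimum time from enrolment to termination: 14 months (Phase II). T1 at 12 months and T2 at 24 months, with transfer after T1 (Time points). Minimum time to expected transfer: 14 months (Subjects). Levels every 4 to 8 weeks (Study endpoints). Recruitment from November 2014 to November 2015, 12 months (Trial status). Planned size: 57 per group, 114 in total (Sample size calculation).

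**The plan's own figure.** With a difference of 0.26 − 0.181 = 0.079, SD 0.15, two-sided 5% and 80% power, n = 2 × (1.960 + 0.842)² × 0.15² / 0.079² ≈ 56.6, so 57 per group. The stated size reproduces. The exact t-test gives 57.6, with 79.6% power at 57. The point below does not depend on it; 114 serves only as the denominator.

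**Step 1: the patient at the limit.** Follow-up is 14 months. T1 is reached (14 − 12 = 2 months to spare). T2 is missed by 24 − 14 = 10 months.

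**Step 2: time left after transfer at the limit.**
- Transfer directly after T1 (month 12): 14 − 12 = 2 months, or 2 × 52.18/12 = 8.7 weeks. That is 8.7/8 = 1.1 to 8.7/4 = 2.2 levels.
- Transfer at the earliest point that the Subjects section expects (month 14): 14 − 14 = 0 months and no levels.

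**Step 3: the primary CV at the limit.** Over 14 months there are 14 × 52.18/12 = 60.9 weeks, which gives 60.9/8 = 7.6 to 60.9/4 = 15.2 levels. The CV is computable and the three-level minimum is met. The share of observation time before transfer is 12/14 = 86% (transfer at month 12) or 14/14 = 100% (month 14). With the full 24 months the corresponding shares are 12/24 = 50% and 14/24 = 58%.

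**Step 4: how many patients might be affected.** The gap between last enrolment and closure is not stated, so it is varied here. Accrual is assumed uniform over 12 months. The share reaching T2 is (12 + gap − 24)/12.

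| Gap from last enrolment to closure | Share reaching T2 | Patients of 114 |
|---|---|---|
| 14 months | 2/12 | 19 |
| 18 months | 6/12 | 57 |
| 20 months | 8/12 | 76 |
| 24 months | 12/12 | 114 |

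On the calendar, if recruitment ends in November 2015, a 14-month gap means closure in about January 2017, whereas the last T2 falls in about November 2017.

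**The case against.** The strongest reply is that this is a slip of wording and that nobody intends to close early. Fourteen months is a minimum, not a closure date. The Time points section gives T2 for both groups at 24 months, the Discussion speaks of outcomes after 12 and 24 months, and the Sample size calculation refers to a complete follow-up period. The same 14 months makes good sense in the Subjects section, as the 12-month T1 plus a margin before transfer. The two timeline figures are not shown and may carry an end date, as may the full protocol behind the article.

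Most of this stands. It makes a slip likely, and it means that nobody can say from this text how many patients would lose T2; the answer could be none. It does not remove the conflict: the Phase II sentence is a stated rule, it disagrees with the visit schedule, and nothing shown overrides it.

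Three stronger readings are tempting and are not supported:

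- **That 95 of 114 patients will have no T2.** This needs both uniform accrual and closure exactly 14 months after the last enrolment. The article states neither.
- **That the primary analysis fails.** One or two post-transfer levels is below three, but the minimum applies to all of a patient's levels, so a patient at the limit on the stated visit schedule would not be coded with the group's largest CV. The power of about 21% that 19 patients would give (normal approximation) applies only to an analysis confined to patients with T2, which is not the planned primary analysis. Unequal follow-up from staggered entry should also fall on both arms alike under stratified block randomization, so it is not in itself a between-arm bias.
- **That post-transfer eGFR and graft survival are lost with T2.** Neither is on the T2 list. eGFR is followed over its course, with data taken from patient files, so these outcomes would be truncated, not absent.

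**Conclusion.** The concern holds as a contradiction in the current text. The enrolment rule admits patients who cannot complete the schedule. Anyone enrolled less than 24 months before termination would miss the T2 questionnaires. At the limit, post-transfer eGFR, graft-survival and drug-level data shrink to between zero and about two months. The primary CV survives, on about 7 to 15 levels, but 86% to 100% of the observation time behind it would lie before transfer, against 50% to 58% with full follow-up.

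The limits of zero and two months follow from the article's own figures, under the two transfer times tried. The number of patients affected does not: it runs from none to 95 of 114 as the gap from last enrolment to closure falls from 24 to 14 months, under an assumed uniform accrual. A drafting slip is the likeliest cause, but the sentence still has to be corrected, because sites enrol by it.

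**What to change.** Reconcile the Subjects, Phase II and Time points sections so that each interval has one stated anchor. Two corrections are open, depending on what was meant:

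1. If the Phase II sentence is meant as an enrolment cut-off, replace the 14 months there with at least 24 months plus the T2 visit window before study termination. Equivalently, set closure no earlier than 24 months (plus that window) after the last randomization.
2. If the 14 months was meant only as the eligibility distance to transfer, keep it in the Subjects section and delete it from the Phase II section.

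The Time points section should also say how transfer after T1 relates to the 14-month distance in the Subjects section; which timing applies is for the investigators to settle.

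**Cost.** If an end date that allows T2 for everyone is already planned, this is a wording correction with no effect on sample size. If closure really was planned earlier, the end date moves by up to 24 − 14 = 10 months (plus any visit window). Levels and eGFR come from routine care without extra blood samples, so the added effort is the T2 questionnaires and the longer data extraction.
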